#### Secondary outcomes

Secondary outcomes include differences of the absolute change in mean depressive and anxiety symptom severity on the PHQ-ADS at 12 months between both study arms. At 6 and 12 months after baseline assessment, we will also calculate the absolute change in mean depressive and anxiety symptom severity on the PHQ-9 and GAD-7, respectively along with differences in mean burden of specific somatic complaints (Somatic Symptom Disorder–B Criteria Scale, SSD-12 [66]), recovery (Recovery Assessment Scale, RAS-G [43]), health-related quality of life (SF-12 questionnaire [67], and EQ-5D 5 L [68]), quality and patient-centredness of chronic illness care (Patient Assessment of Chronic Illness Care–Short Form, PACIC–Short Form [69]), adverse effects (Inventory for the Assessment of Negative Effects of Psychotherapy, INEP [70]), and health service use (Questionnaire for the Assessment of Medical and non-Medical Resource Utilisation in Mental Disorders, FIMPsy [71]) between both study arms. The cost-effectiveness of the primary care embedded MHSVC model of care compared to usual care over the study period will comprise additional secondary outcomes.

### Sample size calculation

Based on the review of the existing evidence, especially of published, sufficiently powered RCTs in the areas of collaborative care [19] and integrated mental health [30, 33, 72] and opinion-seeking within the study team, we chose the absolute change in depressive and anxiety symptom severity on the continuous PHQ-ADS scale from screening (-t1) or, if the baseline assessment has been performed later than 28 days after screening, baseline (t0) to 6 months after baseline assessment (t2 = -t1 + 6 months or t2 = t0 + 6 months, respectively) to be the primary outcome of clinical relevance for patients and health policy makers. For this scale, a reduction of 3 to 5 points is considered clinically relevant and we expect a standard deviation of 9 points [44]. If this reduction is not achieved under the optimised study conditions, it is unlikely that even a minimal significant effect according to Cohen (*d* = 0.2) will be achieved under routine conditions [73]. Statistical tests will be performed at a two-sided significance level of *α* = .05 with a power of 1 − *β* = .80. With these parameters, a sample of *N'* = 292 was obtained. The sample size calculation was performed using PASS 16.0.3. Adjusted for a correlation parameter between baseline and the difference between baseline and post-assessment of *k* = 0.35 (for both intervention and control group) and taking into account 20% loss-to-follow-up (*m* = 0.20) (based on a large study on case management of depression by medical assistants in small German general practices [26]), the required sample size is *N* = (*N'* * (1 − *k*^2^))/(1 − *m*) = 314. For the sake of simplicity, the planning assumes *N* = 320 patients (see Fig. 1 for the study flowchart).

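### The printed N' = 292 fits neither the stated inputs nor the stated 314; N' = 286 fits both, and the planned 320 is unaffected

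*Protocol article*

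**What the plan says.** The whole calculation is in one paragraph of the protocol article (Methods, Sample size calculation).

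- Effect and variability: "a reduction of 3 to 5 points is considered clinically relevant and we expect a standard deviation of 9 points". No single difference is named as the planning value.
- Error rates: "Statistical tests will be performed at a two-sided significance level of *α* = .05", "with a power of 1 − *β* = .80".
- Unadjusted size, from PASS: "With these parameters, a sample of *N'* = 292 was obtained".
- Adjustment for the baseline correlation (k = 0.35) and for 20% loss to follow-up (m = 0.20): "the required sample size is *N* = (*N'* * (1 − *k*^2^))/(1 − *m*) = 314".
- Planned size: "For the sake of simplicity, the planning assumes *N* = 320 patients".

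The Trial design section gives 1:1 allocation.

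**The concern.** The paragraph prints every input, the formula and the result, so anyone can check it, and the check fails. Putting 292 into the printed formula does not give 314, so at least one printed figure is wrong. In addition, 292 is presented as the result of the listed parameters, yet none of the whole-point differences in the stated range (3, 4 or 5 points) leads to it.

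What is at stake is the traceability of the sample-size justification, which the trial report will repeat. The difference the trial was powered for also has to be worked out by the reader. It matters because the same paragraph draws a conclusion about routine care from a failure to reach the reduction, and that argument needs one defined value.

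**Working it through.** **Inputs.** Two-sided alpha .05, power .80, SD 9, relevant difference 3 to 5 points, k = 0.35 and m = 0.20 come from Sample size calculation. The 1:1 allocation comes from Trial design. The planning difference is not stated, so I tried 3, 4 and 5 points.

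**Step 1: the adjustment factor.** 1 − k² = 1 − 0.1225 = 0.8775, and 1 − m = 0.80.

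**Step 2: reproducing 314 from the design inputs.** Two-sample t-test, equal arms, SD 9:

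| Difference | N' (total) | N' × 0.8775 / 0.80 |
|---|---|---|
| 3 points | 286 (142.2, so 143 per arm) | 313.7, so 314 |
| 4 points | 162 | 177.7 |
| 5 points | 104 | 114.1 |

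Three points reproduces the stated 314. The normal approximation for 3 points gives 142 per arm, N' = 284 and 311.5, so 312; the t-test is the version that matches.

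**Step 3: the printed chain.** 292 × 0.8775 = 256.23, and 256.23 / 0.80 = 320.29, so 321 rounded up. That is 321 − 314 = 7 patients above the stated figure (7/314 = 2.2%).

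**Step 4: can 292 be reconciled with 314?**
- Rounding of the inputs is not enough. With k as high as 0.355 and m as low as 0.195, 292 × 0.873975 / 0.805 = 317.0. With m = 0.20, k would have to be about 0.375.
- Inflating by 1 + m instead of dividing by 1 − m gives 256.23 × 1.2 = 307.5.
- Rounding up before the loss step gives 257 / 0.80 = 321.25, so 322.
- Working back, a result of 314 by rounding up needs N' between 313 × 0.80 / 0.8775 = 285.4 and 314 × 0.80 / 0.8775 = 286.3. The only whole number in that interval is 286.

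**Step 5: where 292 might come from.** A standardised difference rounded to 0.33 gives 145.1, so 146 per arm and a total of 292. At SD 9, 146 per arm has 80% power for 2.96 points. The document mentions no such rounding, so this origin is conjecture.

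**Step 6: power of the planned trial.** 320 × 0.80 = 256 analysed, 128 per arm. Residual SD = 9 × √0.8775 = 8.43. For 3 points the t-test power is 0.809 (normal approximation 0.812). At 314 enrolled it is 0.802 (0.805).

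**The case against.** The strongest reply is that nothing of substance follows. The planned 320 gives at least 80% power for 3 points on either reading, the gap is 2.2%, and a reader can recover the planning difference, because 3 is the only whole-point value in the range with an N' anywhere near 292. All of that stands, and it limits the point to a correction of figures. It does not remove the point: the two sides of the printed equation still disagree, and this is neither an effect of condensing the article nor a detail left to an analysis plan, since all the numbers are printed.

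Two stronger readings are tempting and are not supported. A reader might infer that 320 falls short of the trial's own requirement of 321. That takes 292 as right and 314 as wrong, whereas the stated inputs point the other way. Even with 292 accepted, 256 analysed against 256.23 needed is a shortfall of about a quarter of a patient, and 292 without adjustment already has power of 0.81 for 3 points at SD 9. A reader might also infer that a promised margin of six patients has been lost. The document claims no margin; it says only that 320 was chosen for simplicity.

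**Conclusion.** The point holds as an inconsistency in the printed figures. N' = 292, k = 0.35, m = 0.20 and the printed formula give 321, not 314. The most likely error is 292: N' = 286 follows from 3 points, SD 9 and the stated error rates, and it leads exactly to 314. The mismatch itself is certain. Identifying 292 as the wrong figure is an inference, and it rests on a planning difference of 3 points and a t-test calculation, since the PASS output is not shown.

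The consequence is confined to reporting. Power at the planned size is about 0.81 for 3 points, assuming SD 9, k = 0.35 in both arms and 20% loss. The planned 320 does not change.

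**What to change.** In Sample size calculation, state that the planning difference is 3 points, correct N' from 292 to 286, and keep 314 and 320. If 292 was intended, state the effect size that produces it and correct 314 to 321. The PASS output will show which applies.

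In either case, add that 320 enrolled with 256 analysed gives power of about 0.81 for a 3-point difference under the stated assumptions.

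The cost is a corrected sentence or two. No patients are added, and the design and analysis stay as they are.

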**Fig. 1 Fig1:**
[figure not shown]
Study flow chart

### Recruitment

In total, we plan to enrol 320 patients of whom approximately 50% will be allocated to the MHSVC intervention arm. Due the large effort to provide MHSVC for that number of patients at once, we will recruit in three consecutive recruitment waves of approximately 6 months duration and 107 enrolled patients each. Per wave we will enrol approximately ten general practices, so that each of them will recruit ten to twelve patients on average.

#### Study site: general practices

Overall, 30 general practices will be recruited in this trial. First, we will seek to recruit practices by contacting the GPs who expressed interest and/or participated in preceding preimplementation and feasibility studies of the PROVIDE project [17, 39]. Second, we will recruit through the network of collaborating academic research practices affiliated with the Department of General Practice and Health Services Research at Heidelberg University. Finally, we will use contact information from publicly available data bases and registers of the State Board of Physicians of Baden-Wuerttemberg, Hesse, and Rhineland-Palatinate. In those data bases, all within the respective region practising physicians are registered. We will contact practices by mail to introduce the study and establish interest. We will then visit interested practices (1) to underscore how the trial fits with the goals of patient-centred general practice, (2) to evaluate eligibility, (3) to clearly outline the trial and how its procedures may affect the work of the practice, (4) to gain consent to participate, (5) to agree on the regular time slots for the consultations, (6) to hand out the tablet and introduce the videoconferencing platform, and (7) to schedule a virtual get-together between the practice team and the MHS assigned to the practice. Moreover, we will dispense jointly designed brochures and position waiting room posters both tailored to the respective practice. Finally, we will provide practices with a handbook outlining the trial, its procedures (including the handling of the videoconferencing platform), and feasible contingency plans in case of technical failures. This process will continue until enough practices are recruited to obtain the required sample size. We will not enrol any practices prior to obtaining the signed informed consent.

#### Mental health specialists

We will recruit the MHS at the Institute for Psychotherapy, Heidelberg (HIP), which is a state-approved psychotherapeutic training facility at Heidelberg University Hospital. We will contact all lecturers licensed as psychotherapists and all trainees systematically using mailing-lists. All interested individuals will have to apply and will then be invited for a short interview. The final decisions on the participating psychotherapists will be made by mutual discussion and consensus formation in the study team. In total, we will recruit at least 30 psychotherapists or psychotherapy trainees, that is, psychologists in the advanced training period. Each general practice will permanently work together with one MHS only. MHS may participate in more than one recruitment wave. The MHS will participate in the trial as freelancers and will be paid per session according to the current fees for psychotherapy as reimbursed by the German statutory health insurance. For all MHS, expected time expenditure will be approximately 5 h per week (4 h for consultations, 1 h for supervision). All participating MHS will receive a 3-h introductory training, in which we will (1) obtain written informed consent, (2) outline the trial procedures, (3) familiarise MHS with the intervention by walking them through the manual and introducing the context of primary care, and (4) give a step-by-step instruction on conducting video consultations (e.g. room setup and videoconferencing platform,) to foster technical competency which is regarded as crucial for implementing telepsychiatry services [33].

#### Primary care patients

General practitioners will recruit patients during their regular clinic hours or by calling them at home. Based on their clinical judgement, GPs will prospectively select individuals suspected to suffer from depression and/or anxiety and introduce the trial to them by offering information material. We piloted all trial materials and procedures in the feasibility trial concerning user-friendliness. If the patient is interested in participation, she or he will receive the informed consent form and the baseline questionnaire from the GP. The practice team will forward the patient’s contact details to the study team who will screen her or him with respect to the eligibility criteria in a standardised Computer-Assisted Telephone Interview (CATI). At that point, patients will be able to raise questions with the principal investigator who will answer them. The trial participation requires a signed informed consent which the patients will mail back to the trial coordination centre together with the baseline questionnaire. Whenever inclusion is not possible, we will record the reason, the general practice along with patient age and gender. For each patient, the individual intervention period will be three months. Based on our experience from the feasibility trial, we anticipate participant recruitment to take place over approximately 18 months.

### Assignment of interventions

#### Allocation

To minimise reporting and selection bias, baseline measures (PHQ-ADS, SSD-12, RAS-G, SF-12, PACIC–Short Form, FIMPsy, EQ-5D 5 L) will be collected just prior to randomisation. Concerning the PHQ-ADS, however, we will apply screening values for computing the PHQ-ADS change scores, if the baseline assessment has been performed no later than 28 days after screening. After giving written informed consent, eligible participants will then be randomly assigned (1:1) to the intervention or comparison arm via a secure web-based randomisation system (Randomizer V.2.0.2; https://www.randomizer.at) operated by a data manager, not involved in the patient recruitment, centrally at the Institute of Medical Biometry and Informatics, Heidelberg University. Central randomisation will ensure concealment of the treatment sequence up to the allocation. The treatment sequence will be generated through a computer-generated sequence of random numbers. Randomisation will be stratified by general practice and symptom severity at baseline as measured with the PHQ-ADS (three levels: mild, moderate, severe) which we considered as a key prognostic variable for the primary outcome of the trial.

#### Masking

Given the nature of this complex psychosocial intervention, neither GPs nor patients can be blinded to the patients’ allocation to either intervention or comparison arm. As part of the blind outcome assessment, research assistants, masked to participant allocation, will conduct the post-measurement in CATIs with the participants. We will make sure that the outcome assessors will not be present when discussing individual patients and avoid mentioning any names or assigned treatments. In addition, we will instruct patients before the interview not to mention which group, control or intervention, they belonged to. In the case of unintentional unblinding during the assessment, the assessors will document how and at which point the unblinding unfolded. Hence, we will be able to subsequently determine the extent to which blinded assessment was successful.

### Data collection

We will collect participant data from intervention and comparison arms at baseline just prior to randomisation and at 6- and 12-months post randomisation (see Fig. 2 for the study schedule). We will use validated questionnaires presented via an online survey tool (Enterprise Feedback Suite (EFS) Survey, Questback GmbH) and inform all participants that if they decide to withdraw from the study, the data already provided will be retained and used in the analyses unless they request otherwise.

**Fig. 2 Fig2:**
[figure not shown]
Study schedule

### Measures

At baseline, we will assess demographic and clinical characteristics, including age, gender, marital status, education level, employment status, physical health status, chronic medical disease, history of depression/anxiety, current and past psychiatric treatment/psychotherapy, current and past psychopharmacological treatment, willingness to accept psychotherapy, and willingness to accept psychopharmacological treatment.

#### Primary outcome

Depressive and anxiety symptom severity will be assessed at each timepoint using the PHQ-ADS. The PHQ-ADS assesses the 16 symptoms of depression (9 items of the PHQ-9) and anxiety (7 items of the GAD-7) over the last 2 weeks using a 4-point Likert scale (where 0 = “not at all” and 3 = “nearly every day”). Overall sum scores are in the range of 0 to 48, with suggested cut points of 10, 20, and 30 indicating mild, moderate, and severe levels of depression-anxiety symptoms [44, 62, 63]. The PHQ-ADS is a validated diagnostic measure in primary care, with demonstrated efficacy and sensitivity as an outcome measure for treatment trials with a recommended minimally important difference of 3 to 5 points [44].

#### Secondary outcomes

We will assess depression symptom severity and anxiety symptom severity separately using the PHQ-9 and the GAD-7, respectively, which both are subscales of the PHQ-ADS.

We will measure burden of specific somatic complaints using the SSD-12 [66, 74]. The SSD-12 comprises 12 items that require respondents to rate on a 5-point Likert scale how frequently they experience each cognition, emotion, or behaviour (from 0 = “never” to 4 = “very often”). Overall sum scores are in the range of 0 to 48 and provide a three-dimensional measure of the psychological criteria of DSM-5 Somatic Symptom Disorder. The SSD-12 displays high internal consistency (Cronbach’s *α* = 0.94) and good convergent validity, correlating well with measures of somatoform complaints, depression, and anxiety.

Recovery will be measured using the RAS-G [43]. The RAS-G includes 14 items that are rated on a 5-point Likert scale (from 1 = “totally disagree” to 5 = “strongly agree”). The mean scores for the five dimensions (Goal and Success Orientation, No Domination by Symptoms, Personal Confidence and Hope, Reliance on Others, Willingness to Ask for Help) are in the range of 1 to 5 with higher scores indicating better recovery. The RAS-G displays acceptable internal consistency (Cronbach’s *α* from 0.59 to 0.88) and convincing convergent/discriminant validity, correlating positively with other measures of recovery and negatively with several psychopathology measures.

We will assess health-related quality of life using the SF-12 and EQ-5D 5 L questionnaires [67, 68]. The SF-12 is a widely used general health questionnaire that consists of a mental component and a physical component and has demonstrated its psychometric robustness in numerous studies. Overall sum scores are in the range of 0 to 100 with higher scores indicating better quality of life. The EQ-5D 5 L is a standardised instrument for measuring generic health status and comprises five dimensions: mobility, self-care, usual activities, pain/discomfort, and anxiety/depression [68]. The patient rates each dimension on 5 levels: no problems, slight problems, moderate problems, severe problems, and extreme problems. To calculate quality-adjusted life years, the EQ-5D preference weights which are EQ-5D health states evaluated with a German tariff are combined with time [75].

The quality and patient-centredness of chronic illness care will be measured using the PACIC–Short Form which consists of 11 items with each item scored on a 5-point Likert scale (from 1 = “no/never” to 5 = “yes/always”) [69]. Overall mean scores are in the range of 1 to 5 with higher scores indicating better outcomes. The PACIC-Short Form has high internal consistency (Cronbach’s *α* = 0.87) and convergent validity with the established 20-item PACIC.

We will measure adverse effects using the INEP [70]. The INEP comprises 21 items that are rated in a 7-step bipolar format (–3 = “definitely a negative effect” to 3 = “definitely a positive effect”) to detect not only deteriorations but also improvement or lack of change and to prevent negative priming. If a bipolar format is not appropriate to the content, a 4-stage unipolar response format is applied instead (0 = “disagree/not applicable” to “3 = fully agree”). For each item, the attribution is stated from the patient’s perspective (“What caused this outcome?” – “the therapy” or “other circumstances in life”). Only negative effects that are attributed by the patient directly to the psychotherapeutic treatment are considered for the analysis.

Health service use will be measured using the FIMPsy questionnaire which is particularly suited for patients with mental disorders [71, 76]. It assesses the following services in the preceding 6 months retrospectively: psychiatric counselling, assisted living, and occupational integration. FIMPsy also captures contacts with outpatient and inpatient medical providers as well as the intake of medication.

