The research group PROVIDE (ImPROving cross-sectoral collaboration between primary and psychosocial care: An implementation study on VIDEo consultations, https://www.provide-project.de/ziel-konzept/?lang=en), funded by the German Federal Ministry of Education and Research, focuses on innovative modes for delivering primary care mental health. To explore whether and how mental health specialist video consultations (MHSVC) can be implemented in routine primary care in Germany, i.e. a prototype single-handed practitioner system in particular, we conducted a randomised feasibility trial (PROVIDE-B) enrolling 50 patients with depression and/or anxiety between February and October 2019 [39]. In this feasibility trial, acceptability of MHSVC in terms of treatment retention (87.0%) and attendance at sessions (94.4%) was high. Moreover, the nested qualitative study showed that satisfaction was high both in patients and health professionals [40]. Study procedures, e.g. inclusion process, data collection, study monitoring, and appointment management proved to be feasible. Therefore, as the next step, a sufficiently powered randomised controlled effectiveness trial was planned.

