### Objectives

The PROVIDE-C randomised controlled trial (RCT) aims to evaluate whether MHSVC integrated into primary care is a clinically effective and economically efficient treatment in patients presenting with depression and anxiety in comparison to usual care. This paper presents the study protocol for the trial, adhering to the Standard Protocol Items: Recommendations for Interventional Trials (SPIRIT) Statement [41] (see Additional file 2 for the checklist), while the results of the trial will be reported in line with the CONSORT 2010 Statement for Social and Psychological Interventions Statement (CONSORT-SPI 2018) [42].

The primary objective of the PROVIDE-C trial is to study whether MHSVC care compared to treatment as usual is superior in treating primary care patients with depression and/or anxiety. The primary outcome measure is absolute change in depression and anxiety symptom severity at 6 months after baseline assessment. Secondary objectives are to (1) test whether individuals in the intervention arm differ from individuals in the comparison arm in depressive and anxiety symptom severity at 12 months follow-up, burden of specific somatic complaints, recovery (defined as “the personal process of adaptation and development through which the individual overcomes the negative personal and social consequences of [a] mental disorder and regains a self-determined and meaningful life” [43]), health-related quality of life, quality and patient-centredness of chronic illness care, and adverse effects at six and 12 months and (2) evaluate the cost-effectiveness of the primary care embedded MHSVC model of care compared to usual care.

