Patients will receive their first video consultation shortly after randomisation and will be scheduled for five sessions, lasting 50 min each, in biweekly intervals. The video consultations will be carried out on a secure (i.e. encrypted), web-based secure videoconferencing platform on a subscription basis (arztkonsultation ak GmbH, https://arztkonsultation.de) at fixed time slots which general practice staff and therapists will have agreed on. At the beginning of each consultation, a practice team member will escort the patient to the room designated for video consultations, set up the widescreen (12.3-inch) computer tablet and the videoconferencing platform, if applicable, address the patient’s questions, and then leave the room. After the third session, we will conduct an interim monitoring of the symptoms (using the PHQ-ADS) and feedback these results to the therapist. After the final consultation with the patient, the MHS will send a written case summary to the GP which will be attached to the medical record in the primary care practice and on which, if needed, further decisions on follow-up procedures between GP and MHS can be based. During the trial, the MHS will receive biweekly group supervision led by a senior consultant specialised in both psychiatry and psychosomatic medicine from the Department of General Internal Medicine and Psychosomatics, Heidelberg University.

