#### Comparison arm

Patients allocated to the control group will get the usual care provided by the GP. This may or may not include a referral to an MHS. We expect that most people with depression and/or anxiety disorders are currently treated by their GP only. GPs tend to provide brief counselling and prescribe psychotropic medication rather than conduct psychotherapy as laid out in guidelines [14, 55, 56]. Only every fifth patient with depression is referred to specialised care [4]. There will be no restrictions to the usual treatment by the GP.

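### INEP counts only negative effects attributed to psychotherapy, but is compared between arms that differ in psychotherapy exposure, so the harms comparison leans against the intervention

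*Protocol article*

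**What the plan says.** Under Objectives, the protocol article sets out to "test whether individuals in the intervention arm differ from individuals in the comparison arm" on a list of outcomes that includes adverse effects at 6 and 12 months. The Outcomes section (Secondary outcomes) names the INEP as the instrument and places it among the differences between the two study arms. The Abstract also promises a comparison of adverse effects with usual care.

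The Measures section (Secondary outcomes) describes the scoring. For each item the patient names the cause, either the therapy or other circumstances in life, and "Only negative effects that are attributed by the patient directly to the psychotherapeutic treatment are considered for the analysis".

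On exposure, the Intervention arm section states: "Patients will receive their first video consultation shortly after randomisation and will be scheduled for five sessions, lasting 50 min each". The Comparison arm section states: "We expect that most people with depression and/or anxiety disorders are currently treated by their GP only". It adds that GPs tend to counsel briefly and prescribe rather than conduct psychotherapy, and that "Only every fifth patient with depression is referred to specialised care".

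Under Statistical methods, secondary outcomes are exploratory and analysed in the same way as the primary outcome. The article does not restrict the INEP to treated patients, and it does not say how the INEP is scored for a patient who had no psychotherapy.

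**The concern.** An event counts only if the patient had a psychotherapeutic treatment to blame, and exposure to such treatment is what randomisation assigns. A control patient who gets worse under GP care alone has only one fitting answer, other circumstances in life, and that answer removes the event from the analysis. An intervention patient with the same course can attribute it to therapy and be counted.

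The reported difference can therefore show an excess in the intervention arm even when total negative change is equal in both arms or lower under the intervention. The Dissemination policy commits the trial to the CONSORT extension for adverse effects, so harms results will be published, and readers would probably take this one as a statement about net harm.

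The separate recording of adverse events does not correct the imbalance. The Monitoring section says that all adverse events will be recorded, but the only route it describes is communication with the mental health specialists and their supervision. The Discussion says that these specialists had no contact with control participants.

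**Working it through.** The plan gives no figure for this outcome, so there is none to reproduce. The check asks how large a difference the counting rule creates when the risk per treated patient is the same in both arms.

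**Inputs from the article**
- Planned size 320, allocated 1:1, with 20% loss to follow-up (Sample size calculation, Trial design): 160 × 0.80 = 128 per arm. This is an upper limit, because the Retention section lets non-responders complete the PHQ-ADS alone.
- Intervention exposure e_I: 100% as scheduled. As a lower value, 87%, the treatment retention in the feasibility trial (Background and rationale).
- Control exposure e_C: 20%, from the one-in-five referral figure (Comparison arm). That figure is specialist referral in depression, not psychotherapy received in this trial, so e_C is varied from 0% to 40%.

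**Assumption**
- q, the probability that an exposed patient attributes at least one negative effect to therapy. The article gives no value. The same q is used in both arms, from 5% to 20%.

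**Expected proportions**

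P(at least one counted effect) = exposure × q, so the risk ratio is e_I / e_C and q cancels:
- 100% versus 20%: 1.00 / 0.20 = 5.0
- 87% versus 20%: 0.87 / 0.20 = 4.35
- 100% versus 40%: 1.00 / 0.40 = 2.5
- 87% versus 40%: 0.87 / 0.40 = 2.2 (rounded)
- e_C = 0%: no control patient can contribute an event

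The same ratio applies to a mean score if unexposed patients score zero and exposed patients have the same mean in both arms. The result therefore does not depend on reducing the INEP to a yes/no event.

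**Chance of two-sided p < 0.05 with n = 128 per arm**

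Power = Φ[(d − 1.96 × SE0) / SE1], where d = p_I − p_C, p̄ is the mean of p_I and p_C, SE0 = √(2p̄(1 − p̄)/n) and SE1 = √(p_I(1 − p_I)/n + p_C(1 − p_C)/n).

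Example with q = 20% and e_C = 20%: p_I = 0.20, p_C = 0.04, d = 0.16, p̄ = 0.12, SE0 = 0.0406, SE1 = 0.0394. Then (0.16 − 1.96 × 0.0406) / 0.0394 = 2.04, and Φ(2.04) = 0.98.

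| e_I | e_C | q | p_I vs p_C | Chance of p < 0.05 |
|---|---|---|---|---|
| 100% | 20% | 5% | 5% vs 1% | 47% |
| 100% | 20% | 10% | 10% vs 2% | 77% |
| 100% | 20% | 20% | 20% vs 4% | 98% |
| 100% | 40% | 5% | 5% vs 2% | 26% |
| 100% | 40% | 10% | 10% vs 4% | 47% |
| 100% | 40% | 20% | 20% vs 8% | 79% |
| 87% | 20% | 10% | 8.7% vs 2% | 67% |
| 87% | 20% | 20% | 17.4% vs 4% | 94% |

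This is a two-proportion approximation that ignores covariates and practice effects. It shows the scale of the artefact and does not forecast the trial's result.

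**The case against.** The strongest reply is that an arm-level excess in therapy-attributed effects is real: it is the burden that patients ascribe to the added treatment. That stands. The outcome can be read as therapy-attributed effects, and it would be too strong to call it uninterpretable. It does not measure net harm, which is how a between-arm comparison of adverse effects will be taken.

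Second, worsening in controls is not lost to the trial. PHQ-ADS, PHQ-9, GAD-7, SSD-12, RAS-G and the quality-of-life scales are compared between arms whatever the cause. That also stands, and it limits the damage to the adverse-effects outcome itself. Mean differences on those scales do not show how many patients deteriorated, however.

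Third, a reader might infer that the rule fixes the result, with a control count of zero. The article does not support this. Controls may be referred, may continue treatment they had at entry, may have entered with insufficient psychotherapy, and can consult psychotherapists directly. A control might also take the therapy to mean GP treatment.

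Fourth, a reader might infer that the planned model cannot be fitted because the INEP is absent from the baseline measures. That does not follow. The covariates listed under Statistical methods include baseline symptom severity but no baseline INEP, and the INEP is listed as a between-arm difference, which needs no baseline value.

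Finally, secondary analyses are exploratory and patients cannot be blinded in any case. Both are true. The exploratory label lowers the stakes but does not remove a bias built into the definition. Lack of blinding affects every patient-reported outcome and is not specific to this rule.

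**Conclusion.** The concern holds for the direction of the comparison. The stated rule makes the INEP difference largely a reflection of psychotherapy exposure, biased towards more apparent harm in the intervention arm, and it omits worsening in controls who had no psychotherapy.

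The size is uncertain. With equal risk per exposed patient, the apparent excess is about 5-fold at 20% control exposure and 2.5-fold at 40%. The chance of nominal significance ranges from about one in two (q = 5%) to near certainty (q = 20%) at 20% control exposure, and it is lower when more controls have psychotherapy. These figures rest on an assumed q, on a referral figure standing in for psychotherapy received, and on at most 128 patients per arm. They do not support a claim that a significant excess is inevitable.

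The primary outcome and its conclusion are unaffected. The point should be settled before analysis, because otherwise the trial's patient-reported adverse-effects comparison invites a conclusion that it cannot carry.

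**What to change.** Base the between-arm INEP comparison on negative change regardless of attributed cause, restricted to items that patients in both arms can answer. The article does not list the items, so the statistical analysis plan should name them before the data are unblinded. Add the proportion in each arm whose PHQ-ADS worsens by at least 5 points from baseline; the cost-effectiveness analysis already uses a 5-point change on this scale.

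Report therapy-attributed negative effects descriptively, by arm, among patients who received psychotherapy, with a statement that they are not a measure of net harm. The health service use questionnaire, which covers outpatient contacts, may help to identify recipients in the control arm; whether it is detailed enough should be checked.

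The cost is wording in the analysis plan. The items, the attributions and the PHQ-ADS are already collected. The drawback is that an all-cause INEP count departs from the instrument's attribution-based count and is less specific to therapy, which is why the attributed effects should still be reported alongside it.
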